# Dealing with daily challenges in dementia (deal-id study): effectiveness of the experience sampling method intervention ’Partner in Sight’ for spousal caregivers of people with dementia: design of a randomized controlled trial

**DOI:** 10.1186/s12888-016-0834-5

**Published:** 2016-05-11

**Keywords:** Dementia, Caregiver, Support, ESM intervention, RCT

## Abstract

**Background:**

There is an urgent need for psychosocial interventions that effectively support dementia caregivers in daily life. The Experience Sampling Methodology (ESM) offers the possibility to provide a more dynamic view of caregiver functioning. ESM-derived feedback may help to redirect caregivers’ behavior towards situations that elicit positive emotions and to increase their feelings of competence in the caretaking process. This paper presents the design of a study that evaluates the process characteristics and effects of the ESM-based intervention ‘Partner in Sight’.

**Methods/design:**

A randomized controlled trial with 90 spousal caregivers of people with dementia will be conducted. Participants will be randomly assigned to the experimental (6-week ESM intervention including feedback), pseudo-experimental (6-week ESM intervention without feedback), or control group (care as usual). Assessments will be performed pre- and post-intervention and at 2-, and 6-month follow-up. Main outcomes will be sense of competence, perceived control, momentary positive affect, and psychological complaints (depressive symptoms, perceived stress, anxiety, momentary negative affect). In addition to the effect evaluation, a process and economic evaluation will be conducted to investigate the credibility and generalizability of the intervention, and its cost-effectiveness.

**Discussion:**

The potential effects of the ESM intervention may help caregivers to endure their care responsibilities and prevent them from becoming overburdened. This is the first ESM intervention for caregivers of people with dementia. The results of this study, therefore, provide a valuable contribution to the growing knowledge on m-health interventions for dementia caregivers.

**Trial registration:**

Dutch Trial Register NTR4847; date registered Oct 9, 2014.

**Electronic supplementary material:**

The online version of this article (doi:10.1186/s12888-016-0834-5) contains supplementary material, which is available to authorized users.

## Background

Caregivers of people with dementia (PwD) are at great risk of becoming overburdened and of developing psychological and physical symptoms during the caretaking process [1]. This calls for psychosocial interventions that effectively support caregivers of PwD in daily life and help them handling their care responsibilities.

Various psycho-social interventions have been developed in recent years for caregivers of PwD, including psycho-education, emotional support, practical assistance, cognitive-behavioral therapy, and multi-component interventions [2]. Overall, research has shown significant but small effects of current interventions on caregiver outcomes. A common feature in these studies is that outcome measures include retrospective self-assessments that are highly susceptible to emotional and cognitive biases [3]. Moreover, retrospective methods do not provide information about fluctuations in subjective experiences over time and across situations that caregivers of PwD may face due to the continually changing care demands.

The Experience Sampling Methodology (ESM) is an innovative approach in assessing subjective experiences in real-time within the flow of daily life. ESM consists of a structured diary method in which repeated self-assessments are electronically recorded the moment they occur, in their natural setting [4, 5]. ESM offers the possibility to provide a more accurate and detailed view of caregiver functioning, since it enables daily fluctuations in subjective experiences to be explored and it minimizes retrospective recall biases [6, 7]. Therefore, ESM might be a valuable addition to standard retrospective methods, particularly in older populations with an increased incidence of memory deficits [8].

Recently, there has been growing interest in adapting ESM to clinical practice. By using modern technology, such as personal digital assistants (PDAs) and apps, momentary data are immediately available to both caregivers and professionals. This creates the opportunity to develop ESM interventions that provide explicit, visualized feedback on implicit dynamic patterns of feelings, experiences, and behavior [9, 10]. Receiving feedback on behavior can result in emotional and behavioral change, something already known from the field of behavioral therapy [11, 12]. The feedback may help caregivers redirect their behavior towards situations that are conducive to positive emotional experiences. In this way, ESM offers the opportunity to actively involve caregivers in their own empowering process and to provide more personally tailored support [13]. Both these aspects have been demonstrated to be essential in effective psychosocial interventions [14, 15].

A focus on positive experiences facilitates a more positive interaction between the caregiver and the PwD and increases positive emotions in both the parties [16]. According to the ‘broaden-and-build theory’, positive emotions elevate the ability to cope with stressful situations and might consequently help to increase caregivers’ feelings of being capable of caring for the PwD [17, 18]. Positive emotions could thus be an important target in caregiver support interventions, increasing caregiver well-being and reducing long-term negative impacts, such as stress and burden [19, 20].

In a recent study, ESM-derived feedback on positive affect was provided to persons with depression during a 6-week intervention period. Its results showed that personalized feedback increased self-awareness and resulted in a significant decline in depressive symptoms [9]. In another ESM study, in which depressed individuals collected ESM data for scientific purposes but without receiving feedback, some participants reported that responding to the ESM questionnaires had already ‘helped them’ and enhanced their awareness of their daily functioning [21]. So far, few studies have applied ESM in caregivers of PwD in the context of research [22, 23]. Recent evidence suggests that ESM is a feasible method for use with this often elderly and vulnerable population ([name] et al.: Dealing with daily challenges in dementia (Deal-id study): an innovative approach to assess caregiver functioning in the flow of daily life, submitted). However, to date, no ESM interventions have been developed to support caregivers of PwD in dealing with daily challenges associated with dementia. This paper describes the design of a randomized controlled trial (RCT) to evaluate the effects of the ESM-based intervention program ‘Partner in Sight’ for spousal caregivers of PwD.

### Study aims

The specific objectives of the current study are:*Process evaluation* to investigate the internal and external validity of the intervention based on sampling quality (recruitment, randomization, and reach) and intervention quality (relevance, feasibility, and performance according to protocol). The process evaluation will be conducted prior to the effect evaluation in order to provide essential information about credibility and generalizability [24].*Effect evaluation* to assess whether ‘Partner in Sight’ is superior to a pseudo-intervention and control group in terms of producing a clinically significant increase in subjective well-being, as proven by an increase in caregivers’ sense of competence, perceived control, momentary positive affect, and a decrease in psychological complaints (depression, anxiety, stress, and momentary negative affect). A follow-up evaluation will be conducted to examine whether the effects have lasted two and six months after the intervention.*Economic evaluation* to assess the cost-effectiveness of ‘Partner in Sight’ by estimating the impact of the intervention on resource use, costs, and health outcomes.

## Methods and design

The study is a randomized controlled trial with three treatment arms. The experimental condition in which caregivers participate in the ESM-intervention ‘Partner in Sight’ (ESM data collection including feedback) will be compared with a pseudo-experimental condition (ESM data collection without feedback) and a control group (care as usual). Data will be collected pre- and post-intervention and at two- and six-months follow-up (Fig. 1).

**Fig. 1 Fig1:**
[figure not shown]
CONSORT flow diagram

### Study population

The study population will consist of spousal caregivers of community dwelling people with all subtypes and stages of dementia. No age limit will be applied. Participants will be recruited in memory clinics (Maastricht University Medical Center + (MUMC+), Atrium Medical Center Parkstad), ambulatory mental health care institutions (Virenze-RIAGG Maastricht, Lionarons GGZ), dementia day care centers (Sevagram, NOVIzorg, Orbis Glana, Proteion, care farm Ransdalerveld), and caregiver support services (Hulp bij Dementie, Steunpunt Mantelzorg) in the southern region of the Netherlands, and via the website of the Dutch Alzheimer Society. The clinician or care counselor who is involved in the treatment of the PwD will approach caregivers to participate in the study. Subsequently, potential participants will be contacted and screened by the researcher to make sure that they fully meet the following inclusion criteria: (1) being a spousal caregiver of a person with a diagnosis of dementia; (2) sharing a household with the PwD; and (3) informed consent obtained. Exclusion criteria will be: insufficient cognitive abilities to engage in ESM; being overburdened or having severe health problems based on clinical judgment of a knowledgeable practitioner; taking care for a PwD caused by Human Immunodeficiency Virus (HIV), acquired brain injury, Down syndrome, chorea related to Huntington’s disease or alcohol abuse.

### Randomization

Caregivers will be randomly assigned to the experimental group, pseudo-experimental group, or control group. Randomization will be computer-generated and conducted by an independent statistician. Block randomization will be performed to diminish the risk of an unbalanced assignment to the three treatment arms. Randomly permuted blocks with variable block sizes (3, 6, and 9) will be used, by which the block size and specific order will be chosen randomly at the beginning of each block. This reduces the risk of predicting group assignment and keeps research staff blind to the randomization process. The design of this study is single-blind. An independent research assistant, who is being blinded to the treatment allocation, will conduct the baseline, post-intervention and follow-up assessments, and will be asked to evaluate success of blinding and reasons for possible unmasking on the Case Record Form.

### ESM procedure

ESM will be carried out using the PsyMate, an electronic touchscreen device that is specifically designed to monitor experiences and behavior in daily life and that offers the possibility to provide immediate ESM-derived feedback (www.psymate.eu). The PsyMate has been extensively studied and refined in several studies concerning psychiatric populations (e.g. psychosis and depression) [10, 13]. In a recent ESM study with spousal caregivers of PwD, the PsyMate was considered to be a user-friendly and easily accessible device ([name] et al.: Dealing with daily challenges in dementia (Deal-id study): an innovative approach to assess caregiver functioning in the flow of daily life, submitted).

The PsyMate will be programmed to generate ten beeps (sound and vibration) per day at random intervals between 7:30 AM and 10:30 PM. ESM will be used as an assessment tool during the baseline assessment (three consecutive days = 30 beeps in total) and the post assessment (three consecutive days = 30 beeps in total) to evaluate the effectiveness of the intervention. Furthermore, ESM will be used as an intervention tool during the 6-week intervention period (three consecutive days per week = 10×3×6 = 180 beeps in total). In order to include different days of the week, the PsyMate will beep alternately on Friday, Saturday, and Sunday, or Tuesday, Wednesday, and Thursday during the intervention period.

After each beep, caregivers will be asked to complete a questionnaire presented on the screen of the PsyMate, including current affect (four positive affect and eight negative affect items), self-esteem (four items), physical well-being (four items), as well as current context and activities (daily life activities, social company, location and events). At the end of each questionnaire, caregivers will have to indicate whether the beep disturbed them. Answering all questions will take approximately three minutes per beep ([name] et al.: Dealing with daily challenges in dementia (Deal-id study): an innovative approach to assess caregiver functioning in the flow of daily life, submitted). Additionally, the PsyMate will be programmed to generate a morning and evening questionnaire at the beginning and end of each day. The morning questionnaire consists of six items regarding their sleep quality during the previous night and their current level of energy. The evening questionnaire contains twenty-five items concerning the caregivers’ daily sense of well-being and competence, and neuropsychiatric symptoms in the PwD during that day. Responses will be rated on 7-point Likert scales (ranging from 1 ‘not at all’ to 7 ‘very much’), bipolar scales (ranging from −3 ‘very unpleasant/very unimportant’ to +3 ‘very pleasant/very important’), a Visual Analogue Scale (ranging from 0 ‘worst imaginable health’ to 100 ‘best imaginable health’), and box-checking formats. Responses cannot be corrected afterwards. An overview of the ESM items with corresponding response choices and concepts is presented in the Appendix. The specific items of the ESM questionnaires were developed and selected according to information available from previous ESM studies [25, 26], knowledge about the experiences and situations that caregivers of PwD could be expected to encounter in daily life, and the guidelines for item development created by ESM experts [27]. Moreover, the ESM questionnaires were recently tested in a feasibility study that yielded positive results ([name] et al.: Dealing with daily challenges in dementia (Deal-id study): an innovative approach to assess caregiver functioning in the flow of daily life, submitted).

### Study procedure

#### Baseline assessment (T0)

After the randomization procedure, a baseline assessment (T0) will take place in the caregiver’s home or at the MUMC+ according to their preference. Participants will be asked by the research assistant to sign the informed consent before continuation of the study procedure. Next, a demographical interview will be conducted to assess caregiver and care recipient characteristics. Additionally, caregivers will be asked to participate in a 3-day ESM baseline measurement, starting the day after the baseline assessment. A 30-min briefing will be provided during the baseline assessment to ensure that they fully understand the procedure and how to operate the PsyMate. A demo questionnaire will be presented to familiarize caregivers with the device and a leaflet containing all relevant information regarding the use of the device will be handed out. Finally, the caregivers will be asked to complete a number of retrospective questionnaires at their own convenience as part of the effect evaluation.

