### Statistical analyses

#### Primary and secondary outcome measures

Data will be entered twice to guarantee data integrity. Before the analyses, data will be checked for missing values and handled according to their distribution (missing completely at random, missing at random, or not missing at random), and the ‘intention-to-treat’ principle. Additionally, data will be checked for outliers, and normality. Non-parametric tests will be used in case of non-normality after data transformation. Possible baseline differences in group characteristics will be tested with t-tests for continuous and *χ*^2^-tests for categorical variables.

To investigate changes in the primary and secondary outcomes for each group during the intervention period, an analysis of covariance (ANCOVA) will be performed with outcome at post-intervention as the dependent variable, group (experimental, pseudo-experimental, control) as the between-subject factor, and outcome at baseline and potential confounders (e.g. demographic variables, coping, personality, and quality of the relationship) as covariates. Separate analyses will be conducted for each outcome variable. Group differences in the post-intervention outcome, adjusted for the baseline value, will be examined to test the effectiveness of the intervention. In case group differences are present, the inter-group effect size will be calculated using Cohen’s *d*.

To examine changes in the primary and secondary outcomes for each group during the total study period, a linear mixed model (LMM) for repeated measures will be conducted. Analyses will be performed with group as a fixed between-subject factor (3 levels: experimental, pseudo-experimental, and control group) and time as fixed within-subject variable (4 levels: baseline, post-intervention, two-month follow-up, and six-month follow-up) and first-order interactions as additional fixed factors. The LMM will estimate fixed effects (regression slopes) for change in the intervals during (T0-T1) and after (T1-T2, T2-T3) the intervention period. The intervals will be entered as a categorical dummy variable (3 levels). Potential confounders will be added to the model as covariates. Additionally, coach will be added as a random factor to estimate the variability ascribed to the coach.

All data will be analysed using STATA 12.1 [49]. Tests of significance will report mean change and will be two tailed with *α* set at 0.05.

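### Signed consent and all baseline measures are placed after randomization, in conflict with consent as a screening criterion, and nothing says allocation is withheld from caregivers until T0 is complete

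*Protocol article*

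**What the plan says.** The section Baseline assessment (T0) opens with the order of events: "After the randomization procedure, a baseline assessment (T0) will take place". At that visit, "Participants will be asked by the research assistant to sign the informed consent before continuation of the study procedure". The demographic interview follows. Then "caregivers will be asked to participate in a 3-day ESM baseline measurement, starting the day after the baseline assessment", and finally "the caregivers will be asked to complete a number of retrospective questionnaires at their own convenience". No return date for the questionnaires is given.

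Study population lists, among the criteria that the researcher checks at screening, "3) informed consent obtained".

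The Randomization section states "The design of this study is single-blind" and identifies who is blinded: "An independent research assistant, who is being blinded to the treatment allocation". That person conducts the baseline, post-intervention and follow-up assessments.

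Under Statistical analyses, the ANCOVA covariates are "outcome at baseline and potential confounders", with coping, personality and relationship quality among the examples. The mixed model takes baseline as the first of four time levels. Missing data are to be handled under intention-to-treat.

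**The concern.** The sequence in the T0 section is the reverse of the usual one. A covariate measured before randomization cannot be affected by allocation. One measured afterwards is protected only as long as the person supplying it does not know the arm. Here the caregiver supplies every primary, secondary and momentary affect score. Once told, a caregiver cannot remain unaware of the difference between usual care and six weeks of device use with coach sessions. A blinded assistant does not protect a self-completed form.

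The second issue is consent. Someone who is randomized and then declines to sign has been allocated but contributes no data. Burden differs by arm: the two ESM arms face 180 beeps in the intervention period and the usual-care arm faces none. The Discussion reports that many caregivers declined a lighter six-day ESM study for lack of time. If the arm is known when the signature is requested, refusal could be unequal across arms, and the analysed groups would no longer be the randomized ones.

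**Working it through.** **Order of events, side by side**

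| Step | Section | Position |
|---|---|---|
| Consent as an inclusion criterion | Study population | at screening |
| Computer-generated allocation | Randomization | before T0, per the T0 section |
| Consent signature | Baseline assessment (T0) | at the T0 visit, after randomization |
| Interview | Baseline assessment (T0) | same visit, after signature |
| 3-day ESM baseline | Baseline assessment (T0) | from the next day |
| Questionnaires (both primary outcomes included) | Baseline assessment (T0); Table 2 | in the caregiver's own time, no return date |

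A caregiver cannot satisfy the consent criterion at screening and also consent for the first time after allocation. Agreement at screening with a signature at T0 would reconcile the sections, but the article does not say that this is meant. This part needs no assumption.

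**When caregivers learn their arm.** The article does not say. The two consequences below therefore apply only if the arm is known before signing or before T0 is complete.

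**Consequence 1: distorted baseline.** The plan gives no figure to reproduce here, and the sample size of 90 does not depend on the order. Let the shift be the allocation-induced difference in mean baseline, index arm minus comparator, in SD units. Suppose none of it persists to T1. The adjusted contrast is the T1 difference minus slope × baseline difference, so

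bias = −(slope × shift).

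Neither input is in the documents. With assumed ranges:

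| Slope | Shift 0.1 | Shift 0.2 | Shift 0.3 |
|---|---|---|---|
| 0.3 | −0.03 | −0.06 | −0.09 |
| 0.5 | −0.05 | −0.10 | −0.15 |
| 0.7 | −0.07 | −0.14 | −0.21 |

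A simulation with 22 per arm gave −0.097 (slope 0.5, shift 0.2) and −0.212 (slope 0.7, shift 0.3), in agreement with the formula. If the 0.8 in the Sample size section is read as a standardized mean difference, which it does not state, the range is 0.03/0.8 = 4% to 0.21/0.8 = 26% of it.

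The sign depends on the arm and the direction. On a scale where higher is better, an optimistic baseline in the experimental arm makes the result conservative, and a pessimistic one flatters it. If part of the shift persists to T1, that part is added back and the bias changes.

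**Consequence 2: refusal after allocation.** No refusal figure is given. With assumed refusal q on top of the planned 25% loss, the number left per arm is 30 × (1 − q) × 0.75. Power is for a two-group normal test at a difference of 0.8 SD, two-sided 0.05.

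| q | Left per arm | Power |
|---|---|---|
| 0 | 22.5 | 0.77 |
| 5% | 21.4 | 0.74 |
| 10% | 20.3 | 0.72 |
| 20% | 18.0 | 0.67 |

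Three refusals are 3/30 = 10% of an arm. The power loss is modest; unequal refusal between arms is the more serious possibility.

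**The case against.** Randomized does not mean told. An independent statistician generates the allocation, and the assistant who takes the signature and runs T0 is blinded, so that person should not be able to reveal the arm. T0 is described once for everyone: all caregivers get the device briefing and the 3-day ESM, so the visit itself discloses nothing. If caregivers are told only after T0 is returned, the baseline concern largely falls away. The timing of disclosure may be in the full protocol, and the CONSORT figure is not available to settle the order. All of this stands, and it is why the harms are stated as conditional. Equally, no sentence says that allocation is withheld.

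A reader might infer more than the article supports:

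- **That questionnaires may be completed after the programme has started.** Table 2 labels T0 a pre-test, ahead of the intervention period. The absence of a return date does not show late completion.
- **That the treatment contrast is biased.** No shift is documented. The illustration is also least plausible for experimental versus pseudo-experimental, since both arms get the device and the coach.
- **That intention-to-treat is broken.** That requires randomized caregivers who decline to sign and are then left out. None is reported.
- **That nobody agreed to anything before allocation.** Agreement at screening is a possible reading of the inclusion criterion.

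**Conclusion.** The point holds as a defect in the stated procedure. The T0 section places signature and baseline after randomization, and this does not agree with the screening criterion. Both follow from the text alone.

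Allocation-related distortion of baseline and arm-dependent refusal are risks left open by that order. They materialize only if caregivers know their arm before signing or completing T0, which the article neither states nor rules out. The ANCOVA figure of 0.03 to 0.21 SD in absolute size is illustrative. It rests on the assumed shift and slope ranges and on no persistence of the shift to T1, and it has no fixed direction. The planned sample size is not affected.

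**What to change.** Set the order as: screening; signed consent; T0 interview, 3-day ESM and questionnaires completed and collected; then randomization, or release of the allocation by the independent statistician. Amend the T0 section and the consent criterion in Study population so that they agree.

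The ethics section says in the past tense that participants consented, so enrolment may already be under way. For caregivers already randomized in the written order, state when they learned their allocation relative to signing and to returning T0. Report all randomized caregivers by arm, including any who did not sign.

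The cost is a short procedural amendment. Allocation is released a few days later, and some caregivers may leave before randomization. Those losses reduce recruitment yield but do not disturb the comparison between arms. If recruitment is in progress, the trial would contain two sequences, and the report should say which caregivers followed which.
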